**Target Trial Emulation**

| **(A) Research Question** | ***What is the causal effect of exposure to nifedipine on adverse maternal and neonatal outcomes, compared with exposure to labetalol?*** | |
| --- | --- | --- |
|  | **Target Trial (Giant PANDA)** | **Emulation** |
| **(B) Populations** | All women with hypertensive disorders of pregnancy (chronic hypertension, gestational hypertension, or preeclampsia) requiring antihypertensive medication at gestational age 11^+0^-19^+6^; 20^+0^-27^+6^; and 28^+0^-36^+6^.  *Exclusions:* contraindication to labetalol or nifedipine; on both labetalol and nifedipine prior to randomization; unable to provide informed consent; unable to be randomized. | All women with hypertensive disorders of pregnancy (gestational hypertension, chronic hypertension, or preeclampsia) requiring antihypertensive treatment (dispensed labetalol or nifedipine) between 11^+0^ and 36^+6^ weeks’ gestation.  *Exclusions:* Taking both labetalol and nifedipine prior to 11 weeks’ gestation. |
| **(C) Treatment strategies** | Primary  Intention-to-treat (ITT): All women randomized to labetalol or nifedipine, regardless of discontinuation or crossover of treatment groups.    Sensitivity  Per-protocol: All women randomized to labetalol or nifedipine, who continued with assigned treatment until no longer indicated.  On-treatment: All women randomized to labetalol or nifedipine, who continued with assigned treatment until no longer indicated and who self-reported ≥90% adherence across all study contacts. | Primary  Intention-to-treat (ITT): All women who received ≥1 prescription and dispensation of labetalol or nifedipine, including those who received both medications during the study period (crossover will be determined by timing of dispensation) and those who discontinued treatment.  *Crossover defined as receiving both labetalol and nifedipine between 11-36 weeks’ gestation.*  Sensitivity  Per-protocol: All women who received ≥1 prescription and dispensation of labetalol or nifedipine during the study period, but did not receive both medications at any time. |
| **(C) Assignment procedures** | Randomized at diagnosis of hypertension requiring medical intervention (1:1 ratio of nifedipine/labetalol). | “Randomized” (via inverse probability weighting) at point of first dispensation of labetalol or nifedipine during the study period (≥11 weeks’ gestation and ≤36+6 weeks’ gestation). |

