**Developing a causal model using directed acyclic graphs (DAGs) to both identify and summarise causal pathways.**

1. Potential confounders will be determined by the above-named authorship team (a quorum of specialists with expert knowledge). All potential confounders are pre-exposure or at exposure.
   1. Covariates to be included in the selection model:
      1. Type of hypertension (gestational hypertension, chronic hypertension, preeclampsia)*
      2. Maternal diabetes mellitus (yes/no)*
      3. Plurality (1/2+)*
      4. Pre-existing renal disease
      5. Pre-existing autoimmune disease
      6. Maternal smoking during pregnancy
      7. Maternal body mass index
      8. IVF/ART conception
      9. Maternal socioeconomic status (SEIFA quintile)
      10. Maternal age at delivery
      11. Mode of birth (neonatal outcomes only)

*Variables denoted with * are included in the Giant PANDA randomization algorithm.*

**Causal pathway and confounding** (excerpt from Causal Inference, What if. M Hernan & J Robins p85: <https://www.hsph.harvard.edu/miguel-hernan/causal-inference-book/>)

*“...the bias has the same structure: it is due to the presence of a cause (known covariate L or unknown covariate U) that is shared by the treatment A and the outcome Y, which results in an open backdoor path between A and Y. We refer to the bias caused by shared causes of treatment and outcome as confounding…”*

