**Outcome definitions – primary and secondary outcomes.**

1. In the target trial, the **primary maternal outcome** is severe hypertension (systolic blood pressure ≥160mmHg). We do not have reliable access to blood pressure measurements; however, our much larger sample size allows us to investigate downstream effects of severe hypertension (severe morbidity). Therefore, the primary maternal outcome will be a composite comprising:
   1. Maternal mortality (all cause) (yes/no)
   2. Eclampsia (yes/no)
   3. HELLP syndrome (yes/no)
   4. Stroke (yes/no)
   5. Cortical blindness (yes/no)
   6. Retinal detachment (yes/no)
   7. Pulmonary oedema (yes/no)
   8. Placental abruption (yes/no)
   9. Liver rupture (yes/no)
   10. Need for dialysis (yes/no)
   11. Need for extracorporeal membrane oxygenation (ECMO) (yes/no)
2. In the target trial, the **primary perinatal outcome** is a composite of stillbirth (≥20 weeks’ gestation), neonatal death (≤28 days post-birth), and neonatal unit admission requiring separation of the infant and mother. We will maintain this outcome by reporting a primary perinatal outcome comprising:
   1. Stillbirth ≥ 20 weeks’ gestation (yes/no)
   2. Neonatal death ≤ 28 days post-birth (yes/no)
   3. Severe neonatal morbidity, comprising:
      1. Neonatal seizures (yes/no)
      2. Necrotizing enterocolitis (yes/no)
      3. Hypoxic-ischemic encephalopathy (yes/no)
      4. Birthweight <3^rd^ centile (yes/no)
      5. Bacterial sepsis (yes/no)
      6. Intracranial hemorrhage (yes/no)
      7. Neonatal asphyxia
      8. Cardiac arrest (yes/no)
      9. Requirement for mechanical or non-mechanical resuscitation (yes/no)
      10. Requirement for intubation or mechanical ventilation (yes/no)
3. In the target trial, there were several **secondary maternal outcomes** (see *Target Trial Emulation* Table Sfor full list). As these secondary outcomes are largely accounted for in our primary composite outcome, we will report the following secondary outcomes with treatment effect and 95% confidence intervals (CI):
   1. Need for additional antihypertensives (yes/no)
   2. Progression from gestational hypertension to preeclampsia (yes/no)

Additionally, the following outcomes will also be reported in an exploratory capacity (i.e., with summary statistics only):

1. Individual components of the primary outcome (all reported as yes/no)
2. Hospital admission prior to 37 weeks’ gestation (yes/no)

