**PART THREE: SUBGROUP ANALYSES**

Subgroup analyses will be undertaken by:

- Type of hypertensive disorder (chronic hypertension, gestational hypertension, and preeclampsia).
- Per-protocol and complete case analyses.
- Timing of randomization (11+0 – 19+6; 20+0 – 27+6; 28+0 – 36+0).
- Timing of birth (≤34 weeks’ gestation; >34 weeks’ gestation).

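### The per-protocol sensitivity analysis excludes women who received both drugs, which selects on an event after assignment and can produce a difference, or a disagreement with the ITT result, through selection alone

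*SAP*

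**What the plan says.** All of this is in the SAP.

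- **Time zero.** In the Target Trial Emulation table, row (C) Assignment procedures, women are treated as randomized "at point of first dispensation of labetalol or nifedipine during the study period".
- **Primary analysis.** Row (C) Treatment strategies defines the ITT set as "including those who received both medications during the study period". It adds: "Crossover defined as receiving both labetalol and nifedipine between 11-36 weeks" of gestation.
- **Per-protocol sensitivity analysis.** The same row keeps women with at least one dispensation "during the study period, but did not receive both medications at any time".
- **Target trial's per-protocol set.** The neighbouring column describes women "who continued with assigned treatment until no longer indicated". The emulated rule has no continuation condition.
- **Second mention.** Part Three, Subgroup analyses, lists "Per-protocol and complete case analyses" and gives no method.
- **Adjustment.** The section on the causal model states: "All potential confounders are pre-exposure or at exposure". Under (A) Selection model, the propensity weights model the exposure assignment. No section provides for censoring at crossover, weights for crossover, or a caveat on reading the per-protocol result. Under Estimators, every estimator is said to target the same average treatment effect; no separate per-protocol estimand is defined.
- **Blood pressure.** Outcome definitions states: "We do not have reliable access to blood pressure measurements".

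**The concern.** A woman's first drug fixes her arm at time zero. Whether she is in the per-protocol set is normally settled later, by whether the other drug is dispensed. Adding or changing drug may well depend on how her condition develops, which also bears on the outcome. Time matters too: a woman who gives birth soon after her first dispensation has little opportunity to receive the second drug, so she tends to be retained. Retention is therefore linked to gestation at birth, and pregnancy prolongation and preterm birth are among the secondary outcomes.

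Balancing the arms on baseline covariates does not undo a selection made afterwards on unmeasured or evolving severity. If that selection works differently by first drug, the retained groups differ in prognosis even when the drugs have the same effect. Agreement or disagreement with the ITT result could then reflect selection, and a reader could not tell.

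Two details add to the problem. The phrase at any time is wider than the 11 to 36 week crossover window in the same cell, so read literally it could also remove women given the other drug before 11 weeks or after birth. And if the secondary outcome on additional antihypertensives counts the other study drug, which the plan does not define, the exclusion removes those events by construction.

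**Working it through.** **The plan's own figures.** The plan gives no crossover rate, no reason for crossover and no risk among women who cross over, so there is no stated size to reproduce. Its only design figures are in Anticipated sample size: about 7,500 women, split 90/10 (6,750 labetalol, 750 nifedipine), with detectable differences of 3.0 points (maternal) and 5.6 points (neonatal). Power and baseline risks are not stated. With an assumed two-sided 5% test and 90% power, these differences match baseline risks of 5.0% and 25.8%. They are not shown to be wrong, and are used below only for arm sizes and scale.

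**Step 1. One-line calculation under no drug effect.** Let both arms have risk p, let a share c cross over, and let those women have risk r. The risk among women retained is (p − c·r)/(1 − c). Assume p = 6% and r = 12% in both arms, with c = 10% after labetalol and 25% after nifedipine.

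- Labetalol: (0.06 − 0.10×0.12)/0.90 = 5.33%
- Nifedipine: (0.06 − 0.25×0.12)/0.75 = 4.00%
- RR = 4.00/5.33 = 0.75; RD = −1.3 points. With the crossover rates exchanged, RR = 1.33.

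This is sensitive to r. If the larger nifedipine crossover group has r = 9% instead, its retained risk is (0.06 − 0.25×0.09)/0.75 = 5.00%, so RR = 0.94 and RD = −0.33 points.

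**Step 2. Two severity strata, no drug effect.** Assume 30% of women are severe in both arms. Severity is unmeasured and raises both the outcome risk and the chance of crossover. With crossover s₀ (mild) and s₁ (severe), and risks r₀ and r₁:

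retained risk = [0.7(1−s₀)r₀ + 0.3(1−s₁)r₁] / [0.7(1−s₀) + 0.3(1−s₁)]

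Maternal-type outcome: r₀ = 5%, r₁ = 15%, so 0.7×5% + 0.3×15% = 8.0% in each arm with all women kept. Neonatal-type outcome: r₀ = 20%, r₁ = 45%, so 27.5%. Worked example, labetalol 10%/40%: (0.63×0.05 + 0.18×0.15)/0.81 = 7.22%. Nifedipine 5%/15%: (0.665×0.05 + 0.255×0.15)/0.92 = 7.77%.

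| Outcome | Crossover, labetalol (mild/severe) | Crossover, nifedipine (mild/severe) | Retained risk, labetalol | Retained risk, nifedipine | RD (points) | RR | Rejection rate |
|---|---|---|---|---|---|---|---|
| Maternal | 20%/20% | 40%/40% | 8.00% | 8.00% | 0.00 | 1.00 | 5% |
| Maternal | 10%/40% | 10%/40% | 7.22% | 7.22% | 0.00 | 1.00 | 5% |
| Maternal | 10%/40% | 5%/15% | 7.22% | 7.77% | +0.55 | 1.08 | 8% |
| Maternal | 5%/15% | 10%/40% | 7.77% | 7.22% | −0.55 | 0.93 | 8% |
| Maternal | 10%/40% | 20%/60% | 7.22% | 6.76% | −0.46 | 0.94 | 7% |
| Maternal | 10%/60% | 5%/15% | 6.60% | 7.77% | +1.17 | 1.18 | 19% |
| Neonatal | 10%/40% | 5%/15% | 25.56% | 26.93% | +1.37 | 1.05 | 12% |
| Neonatal | 10%/60% | 5%/15% | 24.00% | 26.93% | +2.93 | 1.12 | 37% |

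The rejection rate is that of a two-sided 5% Wald test on the retained numbers, Φ(|RD|/SE − 1.96) + Φ(−|RD|/SE − 1.96), without weighting. It should be 5% under no effect. For the third row, SE = √(0.0722×0.9278/5,467.5 + 0.0777×0.9223/690) = 0.0108 and |RD|/SE = 0.51, which gives 8%.

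**Step 3. Reading the table.** The first two rows show what is needed for a false difference. Unequal crossover alone does not produce one, and neither does crossover that depends on severity in the same way in both arms. The dependence on severity has to differ by first drug. Its sign then depends on which arm loses more of its severe cases.

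**The case against.** The strongest reply is about scope. This is a sensitivity analysis, the primary ITT set keeps women who received both drugs, and nowhere does the plan say that the per-protocol result will support or override the primary conclusion. That stands: a reader might infer that the main result is biased by this rule, and the SAP does not support that.

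A reader might also infer that the rule does remove treatment failures at different rates in the two arms. The document gives no crossover rates or reasons, so this is only a possibility. Early birth limiting the chance to cross over does not by itself imply a difference between arms either.

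Nor is it right that nothing in the plan touches the selection. If the stated estimator is applied to the restricted set, as would be natural, selection through measured baseline predictors such as type of hypertension, diabetes, renal disease, plurality and BMI is handled. What remains is selection on unmeasured or later severity.

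The risk ratios of 0.75 and 1.33 come from one pair of assumed rates. Changing one input moves 0.75 to 0.94, and every false difference shown is smaller than the difference the plan says it can detect. That limits the size but does not remove the distortion: in the two-strata scenarios with a false difference, the test rejected in 7% to 37% of cases instead of 5%.

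Finally, the target trial's own per-protocol definition also selects on behaviour after randomization, and dispensing records do not show when treatment stopped being indicated. The mismatch between the two definitions is real, but the target trial's version is not an unbiased benchmark.

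**Conclusion.** The concern holds in a limited form. The per-protocol set is normally defined by an event after time zero, and the plan corrects for it only through measured baseline covariates. The analysis can therefore show a difference between drugs that do not differ, or disagree with the ITT result through selection alone.

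The size cannot be known from the plan. Under the assumptions shown, maternal-type risk ratios run from about 0.75 to 1.33, with the two-strata scenarios between 0.93 and 1.18. The two-strata risk differences, where not zero, are about 0.5 to 1.2 points (maternal-type) and 1.4 to 2.9 points (neonatal-type) in absolute size, and the direction can go either way. There is no false difference if crossover is unrelated to prognosis or related to it identically in both arms. The crossover rates, the severity share and all risks are assumptions.

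The primary ITT estimate is unaffected by this exclusion. The issue is what the sensitivity analysis can be taken to show, and the sponsor should resolve it before that analysis is interpreted.

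**What to change.** Keep all women and censor each at the first dispensation of the other drug. Weight by the inverse probability of remaining uncensored, from a weekly pooled logistic model with the baseline covariates and time-varying gestation, new diagnoses and admissions. Multiply these by the baseline weights and report standardized RD and RR. Report crossover counts by first drug. State one time window for crossover, and move the analysis out of the subgroup list.

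State two limits alongside the result: residual bias remains because blood pressure, a likely driver of switching, is not reliably available; and censoring at the other drug does not address discontinuation. Call the result supportive only.

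The data cost is small, since the plan already relies on dispensation timing and admission records. The programming cost is larger: the crossover weights have to be re-estimated inside the bootstrap (1,000 samples × 2 imputations = 2,000 fits per analysis), outside the planned *teffects* workflow and with only about 750 women starting on nifedipine. The interval for this analysis will be wider.

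If that is judged out of proportion, the minimum costs almost nothing: relabel the current set as never crossed over, descriptive only; give the crossover counts and the selection caveat; and do not interpret it as a causal check on the ITT result.

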**PROJECT OVERVIEW**

The study will be performed in two parts:

1. The demographic characteristics for women with a hypertensive disorder of pregnancy (i.e., chronic hypertension, gestational hypertension, or preeclampsia) and their infants will be described and compared based on pregnancy exposure to labetalol or nifedipine.
2. By applying a causal framework to the statistical analysis of our observational data, we will determine the *causal effect* of exposure to nifedipine for the management of hypertensive disorders of pregnancy, compared with exposure to labetalol, on maternal and perinatal adverse outcomes. This approach will be used to mimic the conduct of a target randomized controlled trial seeking to recruit pregnant women who require treatment with antihypertensives.
   1. **P**opulation – All women who gave birth in Victoria between 2009 – 2020 and whose pregnancies were affected by hypertensive disorders.
   2. **I**ntervention – Exposure to nifedipine from 11 weeks’ gestation.
   3. **C**ontrol – Exposure to labetalol from 11 weeks’ gestation.
   4. **O**utcome – Adverse maternal and neonatal outcomes (see *Outcome Definitions* below).
   5. **T**iming – From 11 weeks’ gestation until 28 days postpartum.

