| **(D) Follow-up period** | From 11 weeks’ gestation until 28 days post-birth. | From 11 weeks’ gestation until 28 days post-birth. |
| **(E) Outcomes** | **Primary Maternal**  Severe hypertension (systolic blood pressure ≥160mmHg).  **Primary Neonatal**  Composite of stillbirth, neonatal death (until 28 days post-birth), and NICU admission requiring separation of infant and mother (until 28 days post-birth).  **Secondary Maternal**  *Note: Variables denoted with a * are reported with treatment effect and 95% CI, all others are exploratory only and described with summary statistics*.   - Mean antenatal systolic blood pressure* - New diagnosis of preeclampsia* - Severe maternal morbidity (fullPIERS consensus definition)* - Discontinuation of allocated antihypertensive* - Undesirable effects of allocated antihypertensive* - Maternal death* - Indicated birth (induction of PROM)* - Mean antenatal diastolic blood pressure - Proportion of days with antenatal systolic blood pressure ≥140mmHg - Proportion of days with antenatal diastolic blood pressure ≥90mmHg - Diagnosis of eclampsia - Diagnosis of HELLP syndrome - Placental abruption - Components of severe maternal morbidity - Maternal stroke - Prescription of additional antihypertensive drugs - Prescription of alternative antihypertensive drugs - Time from randomization to first discontinuation of allocated antihypertensive - Total number of antenatal hospital inpatient days - Treatment satisfaction - Beliefs about allocated antihypertensive drug - Adherence to allocated antihypertensive drug - Mode of onset of birth   **Secondary Neonatal**  *Note: Variables denoted with a * are reported with treatment effect and 95% CI, all others are exploratory only and described with summary statistics*.   - Major congenital anomaly (as defined by EURO-CAT)* - Birthweight centile* - Need for treatment for neonatal hypoglycemia* - Neonatal unit admission (separation of baby from mother)* - Mode of birth* - Gestational age at birth* - Fetal loss <24^+0^ weeks’ gestation - Fetal loss ≥24^+0^ weeks’ gestation (stillbirth) - Known early neonatal death (up to 7 days post-birth) - Known late neonatal death (7-28 days post-birth) - Principal recorded indication for neonatal unit admission - Length of stay in neonatal unit (and level of care) - Indication for mode of birth - Preterm birth (<37 completed weeks) - Preterm birth (<32 completed weeks) - Birthweight - Birthweight SGA (<10^th^ centile) - Umbilical arterial pH<7 at birth - Apgar score 5min post-delivery - Need for additional resuscitation at birth - Need for respiratory support - Type of respiratory support needed - Type of treatment for hypoglycemia - Lowest blood glucose measurement within 48 hours post-birth - Intracranial hemorrhage - Neonatal seizures - Necrotizing enterocolitis | **Primary Maternal**  Our primary outcome will be a composite of severe maternal morbidity determined by an expert panel, comprising:   - Maternal mortality (all cause) - Eclampsia - HELLP syndrome - Stroke - Cortical blindness - Retinal detachment - Pulmonary oedema - Placental abruption - Liver rupture - Need for dialysis - Need for extracorporeal membrane oxygenation (ECMO)   *Note: We do not have reliable ascertainment of ICU/HDU admission data. By instead including only severe morbidities which can reasonably be attributed to hypertensive disorders, we will provide a more accurate picture of the effect of disease-modifying drugs.*  **Primary Perinatal**  Our primary perinatal outcome will be a composite outcome determined by expert consensus. This will comprise.   - Stillbirth (fetal death ≥20 weeks’ gestation) - Neonatal death (death within 28 days of birth) - Severe neonatal morbidity, including:   - Bacterial sepsis   - Birthweight < 3^rd^ centile   - Cardiac arrest   - Hypoxic-ischemic encephalopathy (HIE)   - Intracranial hemorrhage   - Necrotizing enterocolitis   - Neonatal asphyxia   - Neonatal seizures   - Requirement for intubation or mechanical ventilation   - Requirement for resuscitation (mechanical or non-mechanical)   *Note: We do not have reliable ascertainment of NICU admission data. Many infants who are born following hypertensive pregnancies will be admitted to NICU without any other severe morbidities. By instead including only diagnosed severe morbidities, we will provide a more accurate picture of the effect of disease-modifying drugs.*  **Secondary Maternal**  *Note: Variables denoted with a * are reported with treatment effect and 95% CI, all others are exploratory only and described with summary statistics*.   - Pregnancy prolongation (time from first antihypertensive dispensation to birth)* - Need for additional antihypertensive(s)* - Individual components of the primary composite outcome - Disease progression (new diagnosis of preeclampsia after randomization)   **Secondary Perinatal**  *Note: Variables denoted with a * are reported with treatment effect and 95% CI, all others are exploratory only and described with summary statistics*. *** Indicates core secondary outcome.*   - Preterm birth (<37; <34; <32; and <28 weeks’ gestation)** - Major congenital anomaly (as defined by EURO-CAT)* - Neonatal hypoglycemia* - Respiratory distress - Neonatal hypothermia - Individual components of primary composite outcome - Birthweight <10^th^ centile |

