**Define treatment strategy (exposure), assignment procedures, and follow-up period.**

1. The target trial would randomize at the point of diagnosis of a hypertensive disorder of pregnancy (chronic hypertension, gestational hypertension, or preeclampsia). Women would be randomized in a 1:1 ratio to either labetalol or nifedipine. Follow-up would be until 28 days postpartum, and reasons for drop out would include non-adherence to medication, failure to provide consent, unplanned crossover of participants, and random loss to follow up.
2. In the emulated trial, women will be ‘randomized’ at the point of first dispensation of either labetalol or nifedipine at or beyond 11 weeks’ gestation. We will exclude women who were taking both medications prior to 11 weeks’ gestation (unable to be randomized). We will exclude hypertensive women who received neither labetalol or nifedipine (contraindication or non-indication; this cohort will be described). We will also exclude women without hypertension who received labetalol or nifedipine (this cohort will be described).

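### The maternal outcome window opens at 11 weeks' gestation but treatment is assigned at first dispensation, up to 181 days later, so non-fatal maternal events before treatment fall inside it

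*SAP*

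**What the plan says.** The SAP gives the follow-up period twice. The Timing line of the Project Overview reads "From 11 weeks’ gestation until 28 days postpartum". Row (D) of the Target Trial Emulation table reads "From 11 weeks’ gestation until 28 days post-birth", in the target-trial column and again in the emulation column.

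It also gives the moment of assignment twice. Row (C), Assignment procedures, places it "at point of first dispensation of labetalol or nifedipine during the study period", with a permitted range of 11+0 to 36+6 weeks. The section on treatment strategy, assignment and follow-up says that "women will be ‘randomized’ at the point of first dispensation of either labetalol or nifedipine at or beyond 11 weeks’ gestation".

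The Outcome definitions section introduces the maternal primary outcome with "Therefore, the primary maternal outcome will be a composite comprising" and then lists eleven yes/no items, for example "Placental abruption (yes/no". None carries a date condition relative to dispensation.

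Two secondary outcomes in the table are tied to assignment. Pregnancy prolongation is measured from first dispensation, and the preeclampsia item reads "Disease progression (new diagnosis of preeclampsia after randomization". When Outcome definitions restates progression from gestational hypertension to preeclampsia, as an outcome to be reported with an effect estimate and confidence interval, the words tying it to assignment are gone.

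**The concern.** In a target trial emulation, eligibility, assignment and the start of outcome counting should coincide for each woman. Here the stated window opens at a fixed gestation for everyone, while assignment comes at a date that varies between women. An abruption or stroke in between cannot have been caused by the drug dispensed afterwards, but it may have influenced which drug was chosen. Counting it as an outcome lets cause and effect run backwards, and weighting on baseline covariates does not correct an outcome that is dated before exposure.

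The affected estimate is the effect on the maternal primary composite. The Causal Analysis Structure section lists the follow-up period as step (d) and says that each estimator is defined by steps (c) to (f). By the plan's own rule, then, the window is part of the estimator.

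**Working it through.** **1. Length of the gap.** Inputs: start of follow-up 11+0 weeks (Project Overview; table row D); assignment from 11+0 to 36+6 weeks (table row C).

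- 11+0 weeks = 11 × 7 = 77 days; 36+6 weeks = 36 × 7 + 6 = 258 days.
- Gap = 77 − 77 = 0 days at the earliest, and 258 − 77 = 181 days (25 weeks 6 days) at the latest.

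**2. Does any other rule close the gap?**

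- *Exclusions* (flow chart; table row B; treatment strategy section): use of both drugs before 11 weeks, use of neither drug, and no hypertension. None concerns an outcome event before first dispensation.
- *Adjustment* (covariate list in the DAG section; balance tables for the two primary models): neither includes a prior component event or gestation at start of treatment. The DAG section requires confounders to be pre-exposure or at exposure, but there is no matching post-exposure rule for the primary outcomes.
- *Outcome definitions*: no date condition on any maternal primary component.

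**3. Which outcomes can precede dispensation?**

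| Outcome | Can it fall between 11+0 weeks and dispensation? |
|---|---|
| Non-fatal antenatal maternal components (eclampsia, HELLP syndrome, stroke, pulmonary oedema, abruption, dialysis and similar) | Yes |
| Progression to preeclampsia, as worded in Outcome definitions | Yes, undated there |
| Hospital admission before 37 weeks (exploratory) | Yes |
| Maternal death | No |
| Neonatal death, neonatal morbidity, birthweight, preterm birth | No; these arise at or after birth |
| Stillbirth | Essentially no, apart from one fetus of a multiple pregnancy |

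**4. The plan's own power figure.** Anticipated Sample Size gives detectable differences of 3.0% (maternal) and 5.6% (neonatal) for about 7,500 women split 90/10. It states no alpha, power or baseline risk with them, so they can be neither confirmed nor refuted. Assuming two-sided alpha 0.05, 90% power and groups of 6,750 and 750, a 3.0-point difference corresponds to a labetalol risk of about 5% if nifedipine is higher, or 7.5% if it is lower. At 80% power the corresponding risks are about 7.5% and 9.7%. The timing problem does not depend on this figure; it only suggests a plausible risk for step 6.

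**5. Sensitivity to single events.** Nifedipine group: 7,500 × 0.10 = 750, so one miscounted woman moves the crude risk by 1/750 = 0.13 points. Labetalol group: 7,500 × 0.90 = 6,750, so one woman moves it by 1/6,750 = 0.015 points.

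**6. Illustration; every risk here is assumed.** Observed risk = post-dispensation risk + counted pre-dispensation risk. The labetalol post-dispensation risk is set at 5%.

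| True RR | Pre-dispensation risk, labetalol / nifedipine | Observed risks, nifedipine / labetalol | Observed RR | Observed RD |
|---|---|---|---|---|
| 1.00 | 1% / 2% | 7% / 6% | 1.17 | +1.0 point |
| 1.00 | 2% / 1% | 6% / 7% | 0.86 | −1.0 point |
| 1.00 | 1% / 1% | 6% / 6% | 1.00 | 0 |
| 1.50 | 1% / 1% | 8.5% / 6% | 1.42 | +2.5 points (true value 2.5) |

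Unequal pre-dispensation risks bias both measures, in either direction. Equal ones leave the risk difference alone but pull a non-null risk ratio towards 1.

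**The case against.** The best defence is that 11 weeks marks only the earliest possible entry. Row (D) uses the same words for the target trial, and a randomized trial would not count outcomes before randomization. Elsewhere the plan thinks in terms of individual time zero: assignment at first dispensation, prolongation measured from it, preeclampsia after randomization, and a subgroup by timing of randomization. This reading is plausible, and the authors may well have meant it. But it is written nowhere, and the only window the text gives an analyst of linked records opens at 11 weeks. Anchoring two secondary outcomes and leaving the primary one unanchored does not help.

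Three further points stand and limit the concern.

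- A reader might infer that pre-treatment events have in fact been counted. The document does not show that. It shows a rule that would count them if applied literally; the derivation code may already filter by date.
- A reader might extend the problem to all outcomes, including the perinatal primary composite. Step 3 of the working shows that this composite and maternal death are essentially out of reach.
- A reader might cite preeclampsia before the first prescription as a counted outcome. The table's version already excludes it; only the restatement in Outcome definitions is open. Preeclampsia is not a component of the maternal primary composite.

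**Conclusion.** The follow-up rule is wrong as written, for the maternal primary composite and for two lesser maternal outcomes. The Project Overview and row (D) open the window up to 181 days before the assignment point given in row (C) and in the treatment strategy section, and nothing else in the SAP removes the events in between.

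It would go too far to say that the result is biased by a given amount or towards one drug. The document reports no event dates, no pre-dispensation event rates and no difference in start timing between the drugs. The figures in step 6 show only how the mechanism works under assumed risks. The number of events involved may be small, but with about 750 women on nifedipine, a few would matter.

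**What to change.** 1. In the Project Overview and in the emulation column of row (D), define time zero as the date of first dispensation of labetalol or nifedipine at or after 11+0 weeks, with follow-up from then until 28 days post-birth.
2. In Outcome definitions, count a maternal component only if the event is dated on or after time zero. Use the best available event or diagnosis date, not simply the admission date: a stay that began before dispensation may contain an event that came after it. Apply the same rule to hospital admission before 37 weeks.
3. Restore the after-randomization condition to progression to preeclampsia, so that it agrees with the table.
4. Treat a component event before time zero as baseline history and adjust for it in the models. The composite is a single binary outcome, so dropping a woman from one component is not a workable rule.
5. Add two sensitivity analyses: one excluding women with an earlier component event, and one for events whose timing relative to dispensation is uncertain.

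The cost is some date derivation and a small loss of events. Dispensation timing is already needed for the baseline table, the prolongation outcome and the timing subgroup. If the code already filters on time zero, the window and event rules need only a wording change, with the adjustment and sensitivity analyses added. If it does not, the maternal primary analysis must be rerun.
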